### Immediate and late outcome end-points

The primary outcome end-points will be defined according to the issue investigated in each study. The main immediate outcome end-points of studies from the E-CABG registry are: 1) In-hospital mortality and 30-day mortality, 2) stroke, 3) prolonged use of inotropes, 4) postoperative need of intra-aortic balloon pump (IABP) or extracorporeal mechanical oxygenation (ECMO), 5) immediate repeat revascularization, 6) wound infection and mediastinitis, 7) blood losses and use of blood products, 8) nadir hematocrit, 9) use of prothrombotics, 10) resternotomy for bleeding, 11) atrial fibrillation, 12) acute kidney injury and need of renal replacement therapy, 13) type V myocardial infarction, 14) pericardial effusion requiring treatment, 15) postoperative use of antibiotics, 16) delirium requiring drug treatment, 17) length of stay in the intensive care unit, and 18) length of in-hospital stay. The late outcome end-points of studies from the E-CABG registry are: 1) all-cause mortality, 2) cardiovascular mortality, 3) stroke, 4) myocardial infarction, 5) repeat revascularization and 6) a combined outcome end-point including any of these late adverse events. These end-points and their definition criteria are described in details in the following paragraphs of this article.

### Dissemination policy

The research findings originating from data of the E-CABG registry will be disseminated in the scientific community by presenting the results of these studies in international congresses and publishing them in peer-review international journals in the fields of cardiac surgery and cardiology.

### Steering Committee

The data collection, analysis and writing process will be monitored by the Steering Committee of the E-CABG study. This Steering Committee is formed by a Principal Investigator and a Representative from each of the participating center. Participating centers and investigators are listed in Table 1. The Members of the Steering Committee will take the responsibility for the progress of data collection and its quality through local audit. The Steering Committee will evaluate any study proposal and accept/reject it by voting after having reviewed the study plan and discussed on its feasibility.

### Authorship and the right to use of the registry data

Investigators will be eligible for authorship only if they contributed substantially to study planning, data collection, data analysis and interpretation, writing and critical revision of the manuscripts. In view of the major efforts that each center will face during data collection, one to three authors per each center will be included as main authors of each study performed using the E-CABG registry data. Members of the Steering Committee will decide about any co-authorship from her/his center. The researcher who plans the sub-study, performs the analysis and writes the article will have full right to be the first author of the study. The principal investigator will finalize the database and will guarantee that each Steering Committee Member will have a copy of the overall database as well as of any database created for sub-analyses.

### Research ethics approval

The study has been approved by the local Institutional Review Board or Hospital Chief according to national guidelines for approval of registry studies. Patients’ informed consent is collected in institutions where it is mandatory.

### Schedule

Collection of baseline, operative and immediate postoperative outcome data has started on January 2015 and will end not before December 2015 with a minimum follow-up of 30-days. Follow-up data will be collected during January of each year for ten years. The first analyses of this dataset are expected on July 2015.

### Baseline characteristics and operative data: definition criteria

#### Units of measurements

Units of measurements are likely to differ between centers. In order to avoid any problem during data merging and analysis, laboratory data will be collected according to the suggested units of measurement.

#### Laboratory parameters

Baseline levels of hemoglobin, hematocrit, creatinine, platelets, blood glucose, HbA1c, C-reactive protein, TT-INR and platelets will be collected. Nadir hemoglobin and hematocrit levels as well as highest level of serum creatinine will be recorded as well.

#### Preoperative heart rate and blood pressure

These parameters are obtained in the operating room before anesthesia induction.

#### Preoperative drug treatment

Data on all antithrombotic drugs administered before surgery will be collected. The date of pause of drug treatment refers to the last day the patient received the drug.

Data on any oral or intravenous antibiotics administered preoperatively without prophylaxis purpose, i.e. for any preoperative infectious condition, will be collected.

#### Preoperative *TIA*

Transient ischemic attack refers to any preoperative focal or global neurological syndrome caused by ischemia or hemorrhage resolving within 24 h.

#### Preoperative stroke

Any preoperative focal or global neurological syndrome caused by ischemia or hemorrhage not resolving within 24 h.

#### Poor mobility

Severe impairment of mobility secondary to musculoskeletal or neurological dysfunction.

#### Extracardiac arteriopathy

One or more of the following: claudication, carotid occlusion or >50 % stenosis, amputation for arterial disease, previous or planned intervention on the abdominal aorta, limb arteries or carotids.

#### Diabetes

Diabetes requiring diet, oral or insulin treatment.

#### Hypertension

Arterial blood pressure > 140/90 mmHg or anti-hypertensive treatment.

#### Renal failure

Renal failure will be classified according to the estimated glomerular filtration rate (eGFR) calculated using the Modification of Diet in Renal Disease Study Group modified formula [6]. eGFR for calculation of the EuroSCORE II [7] will be estimated using the Cockcroft-Gault formula [8] according to the criteria of this risk scoring method. The severity of renal failure will be classified in different stages as listed in Table 2.

**Table 2 Tab2:** Stages of renal failure

*Stages*	*eGFR level (mL/min/1.73 m* ^*2*^ *)*
1	90 or above
2	89 to 60
3a	59 to 45
3b	44 to 30
4	29 to 15
5	Less than 15 or on dialysis

#### Dialysis

Peritoneal or hemo-dialysis before surgery.

#### Functioning renal transplantation

Previous renal transplantation with preserved renal function.

#### Chronic lung disease

Any long term use of bronchodilators or steroids for lung disease.

#### Atrial fibrillation

Paroxysmal or persistent/permanent atrial fibrillation before surgery.

#### NYHA functional classes

These are defined according to the criteria listed in Table 3 [9].

**Table 3 Tab3:** New York Heart Association functional classes

*Classes*	*Definition*
I	Cardiac disease, but no symptoms and no limitation in ordinary physical activity, e.g. no shortness of breath when walking, climbing stairs etc.
II	Mild symptoms (mild shortness of breath and/or angina) and slight limitation during ordinary activity.
III	Marked limitation in activity due to symptoms, even during less-than-ordinary activity, e.g. walking short distances (20–100 m). 2Comfortable only at rest
IV	Severe limitations. Experiences symptoms even while *at rest*. Mostly bedbound patients

#### Canadian Cardiovascular Society (CCS) class 4

Inability to perform any activity without angina or angina at rest, i.e., severe limitation.

#### Left ventricular function

Left ventricular ejection fraction recently before CABG (in any case before anesthesia induction).

#### Mitral valve regurgitation

Severity of mitral valve regurgitation before CABG graded in classes from 0 to IV.

#### Systolic pulmonary pressure

Systolic pulmonary pressure measured invasively before anesthesia induction. In case a thermodilution catheter is not inserted, systolic pulmonary pressure will be estimated at echocardiography.

#### Coronary syndrome

Coronary syndrome refers to any of these conditions leading to the present hospital admission for CABG: 1) stable angina, 2) unstable angina requiring or not nitrates infusion, 3) non-ST elevation myocardial infarction, 4) ST-elevation myocardial infarction.

#### Urgency of the procedure

This will be graded according to the criteria listed in Table 4.

**Table 4 Tab4:** Urgency classes of the procedure and their definition

*Urgency*	*Definition*
Elective	Elective procedure for stable angina pectoris
Urgent	Procedure indicated by medical factors which require the patient to stay in hospital to have operation before discharge
Emergency	Procedure performed before the beginning of the next working day after decision to operate. This is further subdivided in four classes:
Emergency class 1	Persistent angina, ECG changes and/or increasing levels of cardiac enzymes despite best medical treatment (nitrates infusion, etc.). No need of inotropes
Emergency class 2	Hemodynamic instability responsive to inotropes
Emergency class 3	Hemodynamic instability unresponsive to inotropes and/or requiring preoperative insertion of IABP
Emergency class 4	Salvage CABG: patients requiring cardiopulmonary resuscitation (external cardiac massage) en route to the operating theatre or prior to induction of anesthesia.
	This does not include cardiopulmonary resuscitation following induction of anesthesia

#### Ventricular arrhythmia

Ventricular tachycardia, ventricular fibrillation or asystole requiring this hospital admission or during hospital stay before CABG.

#### Out-of-hospital cardiac arrest

Cardiac arrest occurred out of the hospital and requiring the present hospital admission for CABG.

#### Critical preoperative status

Ventricular tachycardia or ventricular fibrillation or aborted sudden death, preoperative cardiac massage, preoperative ventilation before anesthetic room, preoperative inotropes or IABP, preoperative acute renal failure (anuria or oliguria <10 ml/hr).

#### Preoperative inotropic support

Preoperative use of epinephrine, norepinephrine, milrinone, amrinone, dobutamine, dopamine, levophed and/or levosimedan.

#### Preoperative use of IABP

Preoperative insertion of IABP before the start of CABG. This refers to any IABP insertion during coronary angiography, percutaneous coronary artery intervention or in the operating room, but before skin incision.

#### Killip classes

These are defined according to the criteria listed in Table 5 [10].

**Table 5 Tab5:** Killip’s stages of heart failure

*Stage*	*Definition*
I	No clinical signs of heart failure
II	Rales or crackles in the lungs, an S_3_, and elevated jugular venous pressure
III	Frank acute pulmonary edema.
IV	Cardiogenic shock or hypotension (measured as systolic blood pressure <90 mmHg), and evidence of peripheral vasoconstriction (oliguria, cyanosis or sweating)

#### CSHA Clinical Frailty Scale

Preoperative patient’s frailty is graded according to the CSHA scale as listed in Table 6 [11].

**Table 6 Tab6:** CSHA Clinical Frailty Scale

*Category*	*Definition*
1	Very fit — robust, active, energetic, well-motivated and fit; these people commonly exercise regularly and are in the most fit group for their age
2	Well — without active disease, but less fit than people in category 1
3	Well, with treated comorbid disease — disease symptoms are well controlled compared with those in category 4
4	Apparently vulnerable — although not frankly dependent, these people commonly complain of being “slowed up” or have disease symptoms
5	Mildly frail — with limited dependence on others for instrumental activities of daily living
6	Moderately frail — help is needed with both instrumental and non-instrumental activities of daily living
7	Severely frail — completely dependent on others for the activities of daily living, or terminally ill

#### Grace score 2.0

This risk score is calculated using the on-line calculator available at http://www.gracescore.org/WebSite/WebVersion.aspx and reported as absolute number [12].

#### Syntax score

This angiographic score is calculated using the on-line calculator available at http://www.syntaxscore.com/[13]

#### EuroSCORE II

This risk score is calculated using the on-line calculator available at http://www.euroscore.org/calc.html and reported in percentage. The risk factors included in the EuroSCORE II and collected in the E-CABG registry are defined according to the EuroSCORE II criteria [7].

#### Previous percutaneous coronary artery intervention

This registry included a number of variables to define accurately any details on previous PCI procedures. Data on the type of stent, either drug eluting or bare metal stents, is collected. Titanium stents are herein considered as bare metal stents. Balloon angioplasty refer to a PCI without stenting. Attempt to PCI with failure to pass the wire/stent through the occlusion/stenosis should not be considered as an accomplished PCI procedure. On the contrary, any PCI attempt resulting in coronary artery complication (thrombosis, dissection, perforation, etc.) should be considered as a prior PCI procedure. Details on PCI-related complications are retrieved as well.

#### Indication for CABG after PCI

The indication for CABG after any PCI procedure is defined as 1) stent thrombosis, 2) in-stent restenosis and/or 3) progression of disease.

#### CABG after PCI

Planned CABG after PCI is defined as a staged procedure in patients whose culprit lesions are treated first by PCI and in whom coronary surgery is planned to achieve complete myocardial revascularization immediately or shortly after PCI. Unplanned CABG refers to any surgical revascularization after PCI which was intended to provide definitive invasive treatment for coronary artery disease.

#### Number of diseased vessels

This refers to the number of vessels (one to three) with a stenosis of at least 50 % in the main artery (the left anterior descending artery, the circumflex artery and the right coronary artery) or their major branches.

#### Left main stenosis

This is defined as any stenosis ≥50 % of the left main trunk.

#### Equivalent to left main stenosis

This is defined as stenoses ≥70 % in the proximal segment of both the left anterior descending artery and the circumflex artery.

#### Antibiotic prophylaxis

Data on type and dose of antibiotics administered prophylactically immediately or during surgery are collected.

#### Off-pump surgeon

This refers to surgeons who have operated in the preceding year at least on 20 patients using the off-pump technique.

#### Revascularization technique

Methods of revascularization are reported in Table 7.

**Table 7 Tab7:** Revascularization techniques

*Technique*	*Definition*
On-pump	Procedure carried out with the use of cardiopulmonary bypass and cardiac arrest
Off-pump	Procedure carried out without the use of cardiopulmonary bypass and cardiac arrest
Heart beating using cardiopulmonary bypass (HB-CPB)	Procedure carried out on beating heart with the use of cardiopulmonary bypass (without cardiac arrest)
Conversion to HB-CPB	Any conversion from off-pump to HB-CPB
Conversion to on-pump	Any conversion from off-pump to conventional surgery with the use of cardiopulmonary bypass and cardiac arrest

#### Epiaortic ultrasound

This refers to epiaortic ultrasound performed to investigate the status of the ascending aorta.

#### Diseased ascending aorta

This is defined as any sign of atherosclerosis in the ascending aorta at palpation or epiaortic ultrasound.

#### Porcelain aorta

This is defined as an extensive circumferential calcification of the ascending aorta.

#### Other intraoperative data

Details of the type of grafts used, number of distal anastomoses, the type of cardioplegia and its temperature as well as the duration of aortic cross-clamping, cardiopulmonary bypass and operation are collected.

#### Drug treatment at discharge

Data on treatment with aspirin, clopidogrel, ticagrelor, warfarin/Coumadin, low-molecular weight heparin, statins and/or ACE-inhibitors are collected.

### Postoperative adverse events: definition criteria

#### Prolonged use of inotropics (>12 h)

This refers to the use of use of epinephrine, norepinephrine, milrinone, amrinone, dobutamine, dopamine, levophed and/or levosimedan for > 12 h after surgery.

#### IABP

This refers to postoperative insertion of an intra-aortic balloon pump device.

#### ECMO

This refers to intra- or postoperative insertion of an extracorporeal mechanical oxygenation device.

#### Resternotomy for bleeding

This refers to any reoperation for hemostasis/removal of hematoma in presence of excessive bleeding with or without hemodynamic problem.

#### Resternotomy for hemodynamic problems

This refers to any reoperation for hemodynamic problems. This can be associated also with excessive bleeding: in such a case, both categories (Resternotomy for bleeding and Resternotomy for hemodynamic problems) are marked.

#### Sternal and leg wound infections

Wound complications are graded according to the Centers for Disease Control and Prevention definitions of surgical site infections [14]. Any sternal or leg wound infection occurring within three months after surgery will be considered as postoperative wound infections.

#### Postoperative atrial fibrillation

It refers to any event of atrial fibrillation/flutter occurred after CABG and detected at ECG, requiring or not pharmacological/electrical cardioversion. Postoperative atrial fibrillation is defined paroxysmal if it is not detected at patient’s discharge. Otherwise atrial fibrillation is defined as permanent.

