## Methods

### Setting, design, study population, patient recruitment and study period

The E-CABG is an observational registry study and its data are prospectively collected consecutively from 13 centers of cardiac surgery of either university or community hospitals located in six European countries (England, Finland, France, Germany and Italy) (Table 1). Patients aged > 18 years undergoing isolated primary or redo CABG for stable coronary artery disease or acute coronary syndrome are eligible for inclusion in this prospective registry. Patients undergoing any other major cardiac surgery procedure will be excluded from this registry. However, patients who undergo CABG associated with Maze will be included in this registry. Patients are recruited in a consecutive series from each institution and their data collected in a specifically created Access-datasheet. The minimum recruitment period is 12 months (January 1 - December 31, 2015). Patients will be followed up after surgery for the following 10 years.

**Table 1 Tab1:** Participating centers and steering committee members of the E-CABG multicenter trial

	*Participating centers*	*Steering Committee Member*	*Other Investigators*
1	Department of Surgery, Oulu University Hospital, Oulu, Finland	[name], *Principal investigator*	[name]
			[name]
2	Department of Cardiac Surgery, Verona University Hospital, Verona, Italy	[name]	[name]
3	Division of Cardiac Surgery, Ospedali Riuniti di Trieste, Trieste, Italy	[name]	[name]
			[name]
4	Cardiac Surgery Unit, Ferrarotto Hospital, University of Catania, Catania, Italy	[name]	[name]
5	Department of Cardiac Surgery, Klinikum Nürnberg, Paracelsus Medical University, Nuremberg, Germany	[name]	[name]
6	Department of Cardiac Surgery, Leicester University Hospital, Leicester, UK	[name]	[name]
			[name]
7	Department of Thoracic and Cardio-Vascular Surgery, University Hospital Jean Minjoz, Besançon, France	[name]	[name]
8	Department of Molecular Medicine and Surgery, Department of Cardiothoracic Surgery and Anesthesiology, Karolinska Institutet, Karolinska University Hospital, Stockholm, Sweden	[name]	[name]
9	Unit of Cardiac Surgery, Department of Cardiosciences, Hospital S. Camillo-Forlanini, Rome, Italy	[name]	[name]
10	Division of Cardiothoracic and Vascular Surgery, Pontchaillou University Hospital, Rennes, France	[name]	[name]
			[name]

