#### Highest postoperative creatinine level

It refers to the highest level of serum creatinine detected after surgery during the in-hospital stay.

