#### Acute kidney injury

This end-point is defined as an increase in serum creatinine 1.5 -1.9 times the baseline level or serum creatinine increase≥26.5 μmol/l within seven days after surgery. This definition is according to the KIDGO criteria [16], but it considers only the change of postoperative serum levels of creatinine as outcome end-point. Therefore, acute kidney injury will be classified as listed in Table 9.

**Table 9 Tab9:** Grading of the severity of postoperative acute kidney injury

*Stages*	*Definition*
1	1.5–1.9 times baseline
	OR
	Serum creatinine increase ≥26.5 μmol/l
2	Serum creatinine 2.0–2.9 times baseline
3	Serum creatinine ≥3.0 times baseline
	OR
	Serum creatinine increase ≥353.6 μmol/l
	OR
	Initiation of renal replacement therapy

The need of renal replacement therapy is defined as temporary or permanent (in case the patient dies or is discharged on renal replacement therapy).

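### Postoperative atrial fibrillation has no new-onset condition, so AF present before surgery is scored as a complication; the AKI time window and the RRT score item also need tightening

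*Protocol article*

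**What the plan says.** **Atrial fibrillation.** The section on postoperative AF states: "It refers to any event of atrial fibrillation/flutter occurred after CABG and detected at ECG". It then classifies the event by rhythm at discharge alone: "Postoperative atrial fibrillation is defined paroxysmal if it is not detected at patient’s discharge. Otherwise atrial fibrillation is defined as permanent". The baseline section lists AF as a preoperative variable: "Paroxysmal or persistent/permanent atrial fibrillation before surgery". The eligibility text adds that "patients who undergo CABG associated with Maze will be included in this registry". AF is item 11 of the immediate end-points, and Table 11 gives it 2 points in Grade 1. Neither place adds a condition on preoperative rhythm.

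**Kidney.** AKI is a rise over the patient's own baseline creatinine "within seven days after surgery", and stage 3 in Table 9 can also be met by initiation of RRT. The postoperative creatinine variable is described thus: "It refers to the highest level of serum creatinine detected after surgery during the in-hospital stay". The section on laboratory parameters likewise lists one highest value and mentions no date. A need for RRT is called permanent "in case the patient dies or is discharged on renal replacement therapy". Table 11 gives renal failure needing RRT 7 points in Grade 3. Dialysis is also a baseline variable: "Peritoneal or hemo-dialysis before surgery".

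**The concern.** A postoperative complication should be something that arises after the operation. The AF rule instead counts a state that some patients bring with them. A patient in permanent AF before surgery who leaves hospital in the same rhythm is recorded as having permanent postoperative AF and moves from Grade 0 to Grade 1. A Maze patient whose rhythm has not converted is treated in the same way.

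Three outputs are affected: the reported incidence of postoperative AF, the additive score that the article proposes as a research tool, and any unadjusted comparison between centers or treatment groups that differ in prior AF. The protocol does condition on baseline elsewhere: Table 8 separates patients with normal and elevated preoperative biomarkers when it defines type V infarction.

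The kidney items raise two lesser questions. A seven-day definition sits beside a creatinine peak taken over the whole stay. The RRT score item does not say how patients already on dialysis are handled.

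**Working it through.** The article states no AF, AKI or RRT rate, so there is no figure of its own to reproduce. All rates and creatinine values below are assumptions chosen for illustration. The definitions and scores come from the article.

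**1. Recorded AF rate.** Let p be the share of patients with prior AF, r the new-onset rate in the others, and q the share of prior-AF patients with AF on a postoperative ECG. Under the stated rule:

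recorded rate = (1 − p) × r + p × q

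With r = 0.28 and q = 0.90:

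| p | Calculation | Recorded rate |
|---|---|---|
| 0.05 | 0.95 × 0.28 + 0.05 × 0.90 | 31.1% |
| 0.08 | 0.92 × 0.28 + 0.08 × 0.90 | 33.0% |
| 0.15 | 0.85 × 0.28 + 0.15 × 0.90 | 37.3% |

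**2. Bias in a crude comparison.** With the same r and q in both groups, the spurious difference is (p1 − p2) × (q − r).

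- 15% versus 5% prior AF: 0.10 × 0.62 = 6.2 points.
- 8% versus 5%: 0.03 × 0.62 = 1.9 points.
- 15% versus 5% with q lowered to 0.60, as if many prior-AF patients were paroxysmal or had converted: 0.10 × 0.32 = 3.2 points.

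The bias disappears only if p is balanced or q equals r.

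**3. Share of events that is pre-existing.** If every prior-AF patient is counted (q = 1), the share is p / [p + (1 − p) × r].

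| p | r | Recorded rate | Pre-existing share |
|---|---|---|---|
| 0.03 | 0.20 | 22.4% | 13.4% |
| 0.03 | 0.30 | 32.1% | 9.3% |
| 0.10 | 0.20 | 28.0% | 35.7% |
| 0.10 | 0.30 | 37.0% | 27.0% |

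**4. Additive score.** A patient with unchanged AF and no other event scores 2 instead of 0. At p = 0.08 and q = 0.90, the mean score per patient rises by 0.08 × 0.90 × 2 = 0.14 points.

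**5. AKI window.** Take a baseline creatinine of 80 μmol/l, a highest value to day 7 of 100, and a later peak of 130.

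- To day 7: +20 μmol/l and 100/80 = 1.25 times baseline. No AKI.
- Whole-stay peak: +50 μmol/l and 130/80 = 1.63 times baseline. Stage 1.

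If AKI were derived from the stored peak, this patient would be counted against the seven-day definition and would take the 4 points that Table 11 gives AKI without RRT. For stays of seven days or less the peak lies inside the window. A whole-stay peak below every threshold also rules out AKI on the inpatient creatinine data. The error is therefore confined to longer stays whose stored peak meets a threshold.

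**6. RRT item.** Table 9 requires RRT to be initiated. The Table 11 item does not repeat that condition. If a center recorded maintenance dialysis under it, a dialysis patient with permanent AF and no new event would score 2 + 7 = 9 and fall in Grade 3.

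**The case against.** The strongest reply on AF is that the problem can be repaired in the analysis. Prior AF is recorded, primary end-points are left to each sub-study, and the statistical methods plan multivariable and propensity-score adjustment. A sub-study on AF could exclude or stratify prior AF without new data. This stands as far as it goes: the 6.2-point figure describes a crude comparison with a threefold imbalance in prior AF, and adjustment may remove much of it. Adjustment does not correct the reported incidence, the permanent label or the Table 11 score, which is fixed in advance and carries no baseline condition.

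On the kidney items, the reply limits how far the point reaches. A reader might infer that AKI itself counts renal disease present before surgery. The article does not support that: AKI needs a rise over the patient's own baseline or initiation of RRT, so stable renal failure does not qualify. The wording about discharge on RRT only labels an existing RRT need as permanent; it does not decide whether an event occurred. The natural reading of the Table 11 item may well be new RRT, and what remains is that the text does not say so.

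A reader might also infer that the seven-day window is unworkable because only the whole-stay peak is collected. That goes too far as well. The article calls itself a summary of variables and the datasheet is not shown, so it may hold a date or an AKI field coded at the site. Nothing says that AKI is derived from the stored peak.

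**Conclusion.** The AF point holds. Followed as written, the definition turns pre-existing AF into a postoperative complication in the end-point, in the permanent label and in the score. Its size depends on rates that the article does not give. With prior AF of 3% to 10%, all counted, and new-onset AF of 20% to 30%, about 9% to 36% of recorded events would be pre-existing disease. An unadjusted comparison of 15% with 5% prior AF would differ by about 3 to 6 points with no true effect, for q between 0.60 and 0.90 and r = 0.28.

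The AKI point is a mismatch between two sections. It matters for stays beyond seven days with a stored peak that meets a threshold, and only if AKI is derived from that peak. Its size cannot be estimated from the article. The RRT point is an unstated condition on one score item.

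**What to change.** - **AF.** For end-point 11 and the Table 11 item, define postoperative AF as new-onset AF in patients without preoperative AF. Report patients with prior AF, and Maze patients, separately, and apply the permanent label only to new-onset AF. The baseline flag is already collected; the cost is a slightly smaller denominator.
- **AKI.** Reconcile the AKI section with the section on the highest creatinine. Record the highest value within seven days, or the date of the peak, beside the whole-stay peak, and derive Table 9 from it. If the datasheet already holds this, say so. Otherwise the cost is one field.
- **RRT.** Restrict the Table 11 item and the RRT end-point to newly initiated therapy, in line with Table 9, so that maintenance dialysis is not scored. The preoperative dialysis flag exists, so no new data are needed.
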